### Drop-outs and cancel cycles

Dropout refers to the study participants’ voluntary decision to withdraw from the study due to personal subjective factors. The canceled cycles were those who were forced to cancel the cycles due to endometrial lesions found in TVUS, failure of follicular development or failure of embryo thawing and resuscitation up to 21 days in the cycle. The researchers will make a detailed summary of the number and causes of dropout and cancelation in both groups and completion characteristics within and between groups. Based on our experience, the dropout rate will be up to 15%. If the actual dropout rate is higher than expected, we will discuss the potential bias, analyze the differences between the results and draw conclusions accordingly.

### Statistical analysis and interpretation of data

The intention-to-treat (ITT) analysis includes both dropout and cancelation cycles. The per-protocol (PP) analysis includes all patients who strictly followed the study protocol. In the as-treated analysis, patients who subsequently received LPS but not NC-FET are excluded, however, those who subsequently received LPS from NC-FET until 10 weeks of gestation are included. We measured OPRs and identified differences between groups based on relative risk (RR) and 95 confidence interval (CI). PP analyses will be also performed for all reproductive outcomes.

Continuous data were compared using Student’s *t*-test and results are presented as mean (standard deviation, SD) or median (inter-quartile range, IQR). Categorical data with expected frequencies less than five is assessed using χ^2^ analysis and Fisher’s exact test. *P*-values less than 0.05 is considered statistically significant. Data analysis will be performed using SPSS 26.0 and R 4.1.3. Multivariate logistic regression analysis will be performed to identify variables independently associated with OPR.

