### Randomization

Randomization will be performed by an independent statistician using a computer-generated randomization schedule with block randomization (block size of four) stratified by female age (< or ≥ 35 years) at LH-surge day in NC-FET cycle. Patients will be randomized in a 1:1 ratio to one of the following groups: (i) LPS group: Patients will receive vaginal combined intramuscular P_4_ treatment starting on the day of ovulation. (ii) Non-LPS group: Neither LPS nor any other therapies are administered to patients.

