### Interventions

Frozen-thawed embryo transfer will be performed in NC with spontaneous ovulation. Transvaginal ultrasonography (TVUS) is used to monitor follicular development and endometrial growth. In the late follicular phase, that is, on days 8–12 of the cycle (depending on the length of the patient’s menstrual cycle), when the dominant follicle develops to a mean diameter of more than 14 mm, serum LH level is monitored every other day until the LH surge appeared (21). When the endometrial thickness reaches more than 8 mm and the endometrium is classified as type A or B, embryo transfer is performed 4 days (D3 embryos) or 6 days (D5/D6 blastocysts) after the appearance of the LH surge. If luteinization of unruptured follicles occurs, embryo transfer is canceled. Plasma hCG levels were measured 14 days after embryo transfer.

Patients in the LPS group are given P_4_ sustained-release gel Crinone ^®^ 8% (Crinone, Merck Serono, Switzerland) vaginally, 90 mg/time, once a day and P_4_ injection (Zhejiang Xianju Pharmaceutical Co., Ltd., Zhejiang, China) intramuscularly, 20 mg/vial, twice a day until 14 days after FET (21). For pregnant women, LPS treatment should be continued until 10 weeks of gestation.

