### Outcome measures

#### Primary outcome

The primary outcome is OPR. Ongoing pregnancy is defined as intrauterine pregnancy confirmed by TVUS examination at more than 12 weeks of gestation accompanied by normal fetal heart beats.

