### Non-inferiority design and power calculation

The present study will adopt the non-inferiority design. Due to previous studies showing that NC-FET treated with LPS does not achieve the same outcome as NC-FET treated without LPS, and that treatment without LPS has the advantages of being less costly and less painful. Specifically, we assumed a 10% margin of non-inferiority and a 50% OPR in two arms based on our center’s experience with FET. The number of cases in each group was calculated at 429, according to the design of 1:1 parallel non-inferiority, the unilateral test with alpha = 0.05, and the power of 90%. Assuming a drop rate of 15%, there are 505 cases per group and 1,010 cases for the two groups.

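### Read strictly, the as-treated rule admits LPS-treated women only if their pregnancy survived to 10 weeks, which would inflate their ongoing pregnancy rate

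*Protocol article*

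**What the plan says.** The Protocol article, under Statistical analysis and interpretation of data, describes three analyses: ITT, PP and as-treated. The as-treated rule is one sentence in two halves. The first half is an exclusion: "In the as-treated analysis, patients who subsequently received LPS but not NC-FET are excluded". The second, set against it, is an inclusion: "those who subsequently received LPS from NC-FET until 10 weeks of gestation are included".

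The Interventions section sets how long LPS lasts. The basic course, whose injections are given "twice a day until 14 days after FET", ends at about the time of the pregnancy test. It is then extended for one subgroup: "For pregnant women, LPS treatment should be continued until 10 weeks of gestation". For the comparison group the Randomization section says: "Neither LPS nor any other therapies are administered to patients".

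The primary outcome is "intrauterine pregnancy confirmed by TVUS examination at more than 12 weeks of gestation accompanied by normal fetal heart beats". The Abstract names ITT and PP as the primary strategies and does not mention as-treated.

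**The concern.** How long a woman takes LPS in this trial depends on her pregnancy. A negative test ends the course at 14 days after transfer. A loss before 10 weeks takes a woman out of the subgroup for whom LPS is extended. Only a woman whose pregnancy is still alive receives LPS to 10 weeks. If receipt to 10 weeks decides who enters the as-treated set as LPS-treated, entry depends on nearly reaching the primary outcome.

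Untreated women have no course to complete, so no such filter applies to them. Selection on a post-randomisation event in one group only biases the comparison by construction, here in favour of LPS. The result at stake is a planned analysis that could show a large apparent harm from omitting LPS when there is none, reported beside ITT and PP results that point the other way.

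**Working it through.** **1. The plan's own figure.** Inputs from Non-inferiority design and power calculation: "we assumed a 10% margin of non-inferiority and a 50% OPR in two arms", and "the unilateral test with alpha = 0.05, and the power of 90"%.

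n per group = (1.645 + 1.282)² × [0.5 × 0.5 + 0.5 × 0.5] / 0.10² ≈ 428.2 (with unrounded normal quantiles), rounded up to 429. With 15% dropout, 429 / 0.85 = 504.7, so 505 per group and 1,010 in total. The stated figures reproduce exactly and are not in dispute. The 429 is used below as the number analysed per group.

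**2. Who can meet the 10-week description.**

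| Woman assigned LPS, fully adherent | LPS under Interventions | Meets the 10-week description? |
|---|---|---|
| Negative test | ends 14 days after transfer | no |
| Loss before 10 weeks | no longer pregnant, so no longer in the extended group | no |
| Pregnancy alive at 10 weeks | to 10 weeks | yes |

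**3. Size under the strict reading.** Set the true ongoing pregnancy rate (OPR) at 50% in both groups. Let q be the probability that a pregnancy alive at 10 weeks becomes ongoing beyond 12 weeks. The document does not give q; it is assumed to lie between 0.90 and 1.00.

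- Share of LPS women alive at 10 weeks = 0.50 / q.
- OPR among them = 0.50 / (0.50 / q) = q.
- q = 0.90: LPS set 429 × 0.556 ≈ 238, OPR 90%, difference (no LPS minus LPS) −40 points, RR 0.50 / 0.90 = 0.56.
- q = 0.95: LPS set about 226, OPR 95%, difference −45 points, RR 0.53.
- q = 1.00: LPS set about 214, OPR 100%, difference −50 points, RR 0.50.

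The chance of showing non-inferiority in this set is then about 0, against 90% when nobody is selected out.

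**4. What if some of the other women are kept?** Let f be the share of LPS women without a live pregnancy at 10 weeks who nevertheless stay in the set (also an assumption).

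LPS OPR = 0.50 / [0.50/q + f × (1 − 0.50/q)]

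At q = 0.95:

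| f | LPS OPR | Difference (points) | Chance of showing non-inferiority |
|---|---|---|---|
| 0 | 95.0% | −45.0 | about 0 |
| 0.50 | 65.5% | −15.5 | about 0.1% |
| 0.75 | 56.7% | −6.7 | about 24% |
| 0.90 | 52.5% | −2.5 | about 70% |
| 1 | 50.0% | 0 | 90% |

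The last column is Φ[(difference + 0.10)/SE − 1.645], with SE² = OPR(1 − OPR)/n_LPS + 0.25/429. The bias vanishes only at f = 1, when every woman who stopped LPS after a negative test or a loss is kept.

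**5. If the sentence is about crossovers.** Suppose it refers to women assigned no LPS who later took it. Counting them as LPS-treated only if they continued to 10 weeks still adds survivors to the LPS group, so the direction is the same. The size then depends on how many women cross over, which the document does not give. The figures in steps 3 and 4 do not apply to that case.

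**The case against.** The strongest reply is that the sentence does not set a completion test. It does not say that only these women are included, it names no arm, and it nowhere excludes a woman who stopped after a negative test. Its contrast may simply be between women who had NC-FET and women who did not, with the 10-week phrase as shorthand for the regimen. A set in which nearly every LPS woman is pregnant is so odd that the authors may well not have meant it. This stands in part: the strict reading is one reading and not an established rule. It does not clear the sentence, because on any reading the text fails to place the women who stopped at 14 days, and its only inclusion criterion is one they cannot meet.

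The second reply is that as-treated is not a primary analysis, that ITT and the sample size are untouched, and that the bias makes no LPS look worse. This stands in full and lowers the severity.

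Three stronger readings are tempting and are not supported:

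- **A false claim of non-inferiority.** A reader might infer that the rule could produce one. The bias runs against non-inferiority, so it could not.
- **A modest bias from early losses alone.** A reader might keep women with negative tests, drop only losses before 10 weeks, and obtain 0.50/0.95 = 52.6% to 0.50/0.90 = 55.6% for assumed losses of 5% to 10%. The arithmetic is right, but the document states no such rule: both groups of women fail a 10-week condition equally.
- **The same fault in PP.** PP takes women who adhered strictly to the protocol. Stopping after a negative test is what Interventions prescribes, so these women already qualify.

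**Conclusion.** The concern holds in a limited form. Applied strictly, the as-treated sentence conditions the LPS-treated group on pregnancy survival close to the primary endpoint and imposes nothing comparable on untreated women. On that reading, with no true difference, the LPS rate would be about 90% to 100% against 50%, a spurious gap of 40 to 50 points. This rests on the plan's 50% rate and on the assumption that 90% to 100% of pregnancies alive at 10 weeks become ongoing. If some of the excluded women are in fact kept, the gap shrinks; if only crossovers are meant, its size cannot be computed from the document.

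The mechanism and its direction follow from the text. Whether the authors intended the strict reading does not, so confidence is medium. Because the analysis is not primary and ITT is unaffected, this should be fixed but does not threaten the trial's main conclusion.

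**What to change.** Rewrite the as-treated sentence as follows:

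1. Delete the condition of LPS receipt to 10 weeks.
2. Define the set as all women who had NC-FET, grouped by the LPS they actually received up to a fixed time point that does not depend on pregnancy status (for example, before the pregnancy test), with the same rule for women assigned to either arm.
3. State that stopping LPS per protocol after a negative test or a pregnancy loss never removes a woman from the set.

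The choice of time point decides how a woman who starts LPS later is classified, so it should be fixed before the data are analysed.

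The cost is one reworded sentence, using data already collected. No change to the PP definition, the LPS regimen or the sample size is implied.

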## Abstract

**Introduction:**

Nowadays, frozen-thawed embryo transfer (FET) has become one of the standard treatments for infertility in the field of assisted reproductive technology (ART). Natural cycle FET (NC-FET) has many advantages, such as simplicity and economics, no effect on patients’ menstrual cycles, estrogen and progesterone levels, as well as no interference in endometrial growth and transformation, which is aligned with the natural physiological state of embryo implantation. Nonetheless, there is a controversy regarding the need for luteal phase support (LPS) during NC-FET cycles. The purpose of this study is to assess whether LPS was not inferior to non-LPS in terms of OPR in NC-FET cycles.

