### Objectives

At present, there is no clear evidence to suggest that LPS is required for NC-FET cycles following spontaneous ovulation. Therefore, there is still a fierce debate in clinical practice about whether patients treated with NC-FET should receive LPS. Our hypothesis is that no LPS is not inferior to OPRs in patients treated with LPS.

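### The sample size uses an absolute 10-point margin at one-sided alpha 0.05, but the analysis section reports relative risk with a 95% CI and gives no margin on that scale

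*Protocol article*

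**What the plan says.** **Design.** Under Non-inferiority design and power calculation, the Protocol article states "we assumed a 10% margin of non-inferiority and a 50% OPR in two arms", with "the unilateral test with alpha = 0.05, and the power of 90" per cent. From this it derives 429 per group, then 505 per group and 1,010 in total after allowing for 15% dropout. The scale of the 10% is not named.

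**Analysis.** Under Statistical analysis and interpretation of data, the OPR comparison is described thus: the investigators "identified differences between groups based on relative risk (RR) and 95 confidence interval (CI". The next paragraph lists the t-test, chi-square and Fisher tests and adds that P-values "less than 0.05 is considered statistically significant". The section does not mention the margin, a risk difference, a one-sided limit or a margin for the relative risk.

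**Direction.** The Objectives section gives the hypothesis as "no LPS is not inferior to OPRs in patients treated with LPS". The Introduction paragraph of the abstract has it the other way round: the purpose is to "assess whether LPS was not inferior to non-LPS in terms of OPR in NC-FET cycles".

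**The concern.** A non-inferiority conclusion needs three things to agree: the effect measure, the margin on that measure, and the confidence level of the limit compared with it. Here the design section fixes one combination (absolute difference, 10 points, one-sided 0.05) and the analysis section names another (relative risk, no margin, 95% CI). The analysis section also speaks of identifying differences, whereas the design asks whether a loss of 10 points can be ruled out.

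An analyst who follows the analysis section obtains a relative risk and interval that cannot be set directly against the margin. Someone would then have to convert the margin after seeing the control rate, choose between a 90% and a 95% limit, or fall back on the absence of a significant difference. Each choice can change the trial's conclusion, and the article says that its results may go into practice straight after publication.

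**Working it through.** **Inputs.** From Non-inferiority design and power calculation: margin 10%, OPR p = 0.50 in both arms, one-sided alpha 0.05 (z = 1.6449), power 90% (z = 1.2816), 1:1 allocation, 429 per group, 15% dropout. From Statistical analysis and interpretation of data: relative risk (RR) with a 95% CI (z = 1.9600).

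**1. Reproducing 429, which settles the scale.**
Absolute margin: n = 2p(1-p)(z_alpha + z_beta)² / margin² = 0.50 × (1.6449 + 1.2816)² / 0.10² = 428.2, so 429. Then 429 / 0.85 = 504.7, so 505 per group and 1,010 in total. All the stated figures reproduce.

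For a margin RR0 on the log RR scale, n = [2(1-p)/p](z_alpha + z_beta)² / (ln RR0)². The readings tried were:

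| Reading of the 10% | One-sided alpha | n per group |
|---|---|---|
| 10 points absolute | 0.05 | 429 |
| 10 points absolute, restricted-null variance (Farrington-Manning) | 0.05 | 426 |
| 10 points absolute | 0.025 | 526 |
| 10% of 50%, i.e. 5 points absolute | 0.05 | 1,713 |
| RR 0.90 | 0.05 | 1,543 |
| RR 0.80 | 0.05 | 344 |
| RR 0.80 | 0.025 | 423 |

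Only the absolute 10-point margin at one-sided 0.05 gives 429.

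**2. Interval level.** One-sided 0.05 corresponds to the lower limit of a two-sided 90% CI. At 429 per group the standard error of the risk difference is sqrt(0.50/429) = 0.03414, and 0.10/0.03414 = 2.929.
- 90% CI: power = Phi(2.929 - 1.645) = Phi(1.284) = 90.0%, as planned.
- 95% CI: power = Phi(2.929 - 1.960) = Phi(0.969) = 83.4%.
- 90% power with the 95% CI: 0.50 × (1.9600 + 1.2816)² / 0.01 = 525.4, so 526 per group; 526/0.85 gives 619 per group, 1,238 in total.
- If all 505 per group are analysed and the OPR is still 50%: 0.10/sqrt(0.50/505) = 3.178, so the 95% CI gives Phi(1.218) = 88.8%.

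**3. Scale.** The RR equivalent of a 10-point loss is (p - 0.10)/p for control OPR p. The 40% and 60% values are illustrative assumptions.
- p = 0.40: 0.30/0.40 = 0.75
- p = 0.50: 0.40/0.50 = 0.80
- p = 0.60: 0.50/0.60 = 0.83

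**4. If non-significance were taken as non-inferiority.** Suppose the true OPR is 50% with LPS and 40% without, a loss equal to the margin. The chance of a non-significant two-sided test is Phi[(1.960 × SE_pooled - 0.10)/SE_unpooled].
- 429 per group: SE_pooled = sqrt(2 × 0.45 × 0.55/429) = 0.03397; SE_unpooled = sqrt(0.49/429) = 0.03380; Phi(-0.989) = 16%.
- 505 per group: 0.03131 and 0.03115; Phi(-1.240) = 11%.

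The design allows 5%.

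**The case against.** The strongest defence is that the design section already fixes a non-inferiority question, a margin and a one-sided test, and that a condensed article may leave the exact decision rule to a full protocol or analysis plan not shown here. This stands so far as it goes. A reader might infer that the planned analysis never tests the trial's hypothesis, and the document does not support that. The missing decision rule alone would not be a finding. What remains is a conflict between two things that the article does state: the basis of its sample size, and its effect measure with interval level.

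Four other stronger readings also fail.
- **P<0.05 as the primary criterion.** The text does not say so. The sentence follows the list of general tests and may be only a convention. Nothing says that P≥0.05 will be read as non-inferiority, so the 16% and 11% show what such a reading would cost; they are not properties of a stated rule.
- **The margin as RR 0.90.** This would leave far less than 90% power, but the sample size excludes it: RR 0.90 would need 1,543 per group.
- **The direction of the test in real doubt.** The abstract sentence is reversed, but the Highlights, Objectives and Discussion all make no LPS the arm to be shown non-inferior. It is a slip.
- **ITT and PP without a combining rule.** Naming both is compatible with requiring both, and such a rule is ordinary analysis-plan content.

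It can also be said that RR is workable. At a 50% control OPR, 10 points equals RR 0.80. Testing against that at 429 per group gives -ln(0.80)/sqrt(2/429) = 0.2231/0.0683 = 3.27, hence about 95% power at one-sided 0.05 and 90% with a 95% CI. That is correct, but no such RR margin is fixed in advance, and it equals 10 points only if the control rate turns out to be 50%.

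**Conclusion.** The concern holds as a mismatch of measure and interval level between the design and the analysis section. The sample size is not wrong: 429, 505 and 1,010 all reproduce.

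The effect is moderate in power and potentially larger in interpretation. Carrying the stated 95% level over to the risk difference lowers power from 90.0% to 83.4% at 429 per group. Staying with RR leaves the threshold to move between 0.75 and 0.83 over control rates of 40% to 60%. Treating non-significance as non-inferiority would roughly double or triple the intended 5% error at the margin, to 11% at 505 per group or 16% at 429.

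These figures rest on the article's 50% OPR and normal approximations. The absolute scale is inferred from the exact reproduction of 429, since the text does not name it. An unseen analysis plan may contain the right rule, but the article's two sections would still need to be aligned.

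**What to change.** - **Primary analysis.** State it as the risk difference, OPR(no LPS) minus OPR(LPS). Conclude non-inferiority if the lower limit of the two-sided 90% CI (one-sided 95%, matching alpha 0.05) is above -10 percentage points, in the ITT set and confirmed in the PP set. Say in the sample-size section that the margin is absolute.
- **If the 95% CI is kept for this test.** Restate the power as about 83% at 429 per group, or plan for 526 per group (619 after dropout, 1,238 in total).
- **Supportive results.** Report RR with its 95% CI as supportive, and state that difference tests at P<0.05 do not decide non-inferiority.
- **Minor.** Correct the abstract so that the hypothesis is no LPS non-inferior to LPS, as in the Highlights, Objectives and Discussion.

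With the 90% CI the cost is a few sentences in the analysis section, one clause in the sample-size section and one sentence in the abstract. No further patients or data are needed. The change should be made before outcome data are compared by arm.

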### Patient and public involvement statement

Patients and the public are not involved in developing research questions or study design. The results of the study will be disseminated to the participants and their families by telephone and the patient’s attending physician.

### Ethics and dissemination

This study has received ethical approval from the Reproductive Ethics Committee of the Affiliated Hospital of SDUTCM (SDUTCM-RM-2022076) and all participating hospitals. The researchers had obtained written informed consent from each patient participating in the study before the start of the study. Any amendments to the protocol that could affect the design, conduct, and safety of the study will be implemented after formal amendment by a committee. Data will be reviewed and approved by an external Data and Safety Monitoring Board. Details of data management will be given elsewhere in this paper.

It is sufficiently assured that the trial personnel’s safety is assured. Whether they are administered LPS after NC-FET make the difference between the two regimens. We don’t expect there to be a difference in the OPR between those who receive LPS and those who do not receive LPS. In most cases, the study will not cause discomfort or harm to the patient. When blood is drawn and P_4_ is injected intramuscularly, the patient may feel pain and discomfort and may experience minor bruising. Neither will participants incur additional financial costs nor will they receive financial compensation for participating in the clinical study.

The study will be presented at national and international scientific meetings by presenting the results in scientific journals and the Chinese Clinical Trial Registry (ChiCTR) and published in high impact peer-reviewed international scientific journals for reproductive medicine. The results of the common interest will be reported in the public media.

